#### Exclusion criteria

The exclusion criteria for the interventional study are as follows:
Pregnant or lactating womenPatients who received immunosuppressive or immunoenhancement therapy within the past 3 monthsPatients with a known or suspected autoimmune diseasePatients not expected to survive 28 days due to end-stage disease or other uncorrectable medical conditionFasting subjectsKnown or suspected allergy to any ingredient of SNT

### Blinding and masking

The laboratory technicians and the biostatisticians responsible for the statistical analysis will be blinded to the assigned treatments. They will not be unblinded under any circumstance.

### Sample size determination

There are no previous clinical studies on using SNT to improve immune function in sepsis, and because of the pilot nature of this study, we need to recruit at least 20 participants in each group to achieve sufficient precision for a sample size calculation in a subsequent full trial [17]. With a 20% dropout rate, we plan to recruit a total of 50 participants. Moreover, since participants can withdraw or may be removed from the trial, 52–60 random numbers may ultimately be needed. Thus, the final number of participants in each group may be differ.

### Mechanism of action

*Shufuzi* can form *yang*. It is the “sovereign” ingredient. It is pungent and sweet, and it warms the kidneys. *Ganjiang* is pungent and warm. It is the “minister” ingredient. It can restore *yang* when combined with *shufuzi*. *Zhigancao* reduces tension and alleviates the dryness-heat effects of *shufuzi* and *ganjiang.* It is the “assistant” ingredient. This combination of the three herbs can prevent the collapse of *yang*. Due to the long-term experience and its extensive clinical application, the SNT decoction used in our trials is considered safe and effective for patients with septic shock. However, according to the principles of modern clinical trials, its use has been criticized due to a lack of adequate assessment. Thus, to evaluate the feasibility of testing the efficacy of SNT administration, we designed this randomized controlled pilot trial.

### Standard therapy

Standard therapy is based on current recommendations [1], including antimicrobial therapy, initial resuscitation, fluid therapy, mechanical ventilation, glucose control, sedation or analgesia, renal replacement therapy, and adequate nutrition. Empiric broad-spectrum antimicrobial therapy is administered as soon as sepsis is diagnosed. The optimal dose and the route of administration follow medical standards. In addition, a daily assessment to allow a de-escalation of antimicrobial therapy is recommended. Protective lung ventilation is administered if acute respiratory distress syndrome occurs due to the sepsis, which is defined as a tidal volume of 6–8 mL/kg (predicted body weight), platform pressure <30 cm H_2_O, positive end-expiratory pressure ≥5 cm H_2_O, minimum tolerated oxygen concentration (FiO2), and oxygen saturation of 88–92%.

### Outcomes

The primary endpoint is the feasibility of the study. It will (1) explore the feasibility of recruiting, randomizing, and retaining participants, (2) evaluate the acceptability and compliance of SNT as an intervention alongside usual care, (3) evaluate the appropriateness of secondary outcome measures, (4) generate data for effect size calculations for future trials, and (5) be used to develop an appropriate protocol for further trials. The time required to recruit 50 participants, the recruitment rate, and the dropout rate will be measured. Successful recruitment is defined as at least half (50%) of eligible patients enrolled, with a dropout rate of no more than 20%.

The secondary endpoints include:
28-day all-cause mortality ratesimmune function data: monocyte human leukocyte antigen-DR (mHLA-DR) expression and ratio of CD4+ to CD8+ T lymphocytesinflammation data: CRP, interleukin-6 (IL-6), interleukin-10 (IL-10), procalcitonin, and tumor necrosis factor α (TNF-α) levelsSequential Organ Failure Assessment (SOFA) scoresAcute Physiology and Chronic Health Evaluation (APACHE) II scores

The exploratory outcomes are mortality in the ICU, length of stay in the ICU, hospital mortality, and length of hospital stay. Safety outcomes include a complete blood count, a general urine analysis, C-reactive protein (CRP), liver function tests (alanine transaminase (ALT), aspartate transaminase (AST), alkaline phosphatase (ALP), total bilirubin (TBIL), and gamma-glutamyltransferase (GGT)), and a renal function test (blood urea nitrogen (BUN) and serum creatinine (Scr)), all of which will be performed at days 0 and 3.

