### Data acquisition and assessment of biological data

Participants receive a study ID, which is used to conceal their identity in documents. Investigators involved in this study have access to their actual identity only on an as-needed basis.

The recruitment rate is the percentage of eligible patients who agree to participate in the study. The dropout rate is the percentage of patients who are lost after enrollment up to the 28th day from enrollment, after which no outcome data are collected. Follow-ups are by bedside visit if the patient is still in hospital, or by phone call when a face-to face follow up is not available.

As well as the outcome measures, the following clinical data will be collected from all participants: age, gender, infection source, and co-morbidities. Immune function data, inflammation data, APACHE II scores, and SOFA scores will be collected on the day of enrollment and 3 days after enrollment. The trial schedule is listed in Fig. 2.

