Researchers are trained to collect trial data carefully according to a standard protocol. Molecular biomarkers will be measured in triplicate to ensure quality. All data will be input into an electronic database (REDCap 5.7.0, hosted at Peking Union Medical College Hospital) designed for the study. The data will be entered independently into the database by two researchers and will be checked separately by different trained researchers. All collected data forms will be kept in the hospital’s Scientific Research Department.

All adverse events after enrollment to the 28th day after enrollment, regardless of whether they are related to the intervention, will be recorded. All severe adverse events and unexpected adverse events will be reported to the ethics committee within 1 day. The intervention will be suspended if necessary. Symptomatic treatment will be offered when needed. The principal investigator will decide whether patients affected by adverse events should discontinue their participation.

Data and safety will be monitored by the institutional review board of Guangdong Provincial Hospital of Chinese Medicine and the Scientific Research Department of Guangdong Provincial Hospital of Chinese Medicine, which are independent of the sponsor and have no competing interests.

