### Statistical analysis

Quantitative numerical data with a normal distribution will be presented as mean ± standard deviation, while data with a non-normal distribution will be presented as median and interquartile range. Categorical variables will be expressed as frequencies or numbers. Equality of variances between groups will be assessed by Levene’s test. An unpaired Student’s *t*-test will be used for normally distributed quantitative variables, while the Wilcoxon nonparametric statistic will be used for non-normally distributed variables. Pearson’s chi-squared test or Fisher’s exact test will be used for categorical data when appropriate. Differences in biological metrics between arms over time will be evaluated by repeat measures of a general linear model, if appropriate. An intention-to-treat analysis will be used for data for participants who did not complete the study or the follow-ups after treatment.

*P <* 0.05 will be considered as statistically significant. All statistical analyses will be performed with SPSS (version 17.0, Chicago, USA) for Windows by researchers not involved in implementing the trial.

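### As written, day-3 outcomes and lengths of stay make no provision for death, so planning effect sizes describe survivors only; hospital outcomes may also be cut off at day 28

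*Protocol article*

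**What the plan says.** All references are to the Protocol article.

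- **Day-3 outcomes.** Under Outcomes, SOFA, APACHE II, mHLA-DR, the CD4+/CD8+ ratio and the inflammation markers are secondary endpoints. Under Data acquisition and assessment of biological data, they are taken twice: "APACHE II scores, and SOFA scores will be collected on the day of enrollment and 3 days after enrollment", with the immune and inflammation data on the same two days.
- **Stays.** The Outcomes section continues: "The exploratory outcomes are mortality in the ICU, length of stay in the ICU, hospital mortality, and length of hospital stay". It gives no time window.
- **Tests.** Under Statistical analysis, an unpaired t-test "will be used for normally distributed quantitative variables, while the Wilcoxon nonparametric statistic will be used for non-normally distributed variables". For the markers: "Differences in biological metrics between arms over time will be evaluated by repeat measures of a general linear model, if appropriate". For non-completers: "An intention-to-treat analysis will be used for data for participants who did not complete the study or the follow-ups after treatment". No sentence says how a death enters a day-3 value or a stay.
- **End of data collection.** The sentence that defines the dropout rate, under Data acquisition, runs "up to the 28th day from enrollment, after which no outcome data are collected". The adverse-event window in the same section is "All adverse events after enrollment to the 28th day after enrollment".
- **Purpose.** The feasibility aims under Outcomes include judging whether the secondary outcome measures are suitable and producing effect-size data for later trials.

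**The concern.** In a sepsis trial some patients can be expected to die within days of enrollment. A two-point design has no second measurement for anyone who dies before day 3. A t-test or Wilcoxon test at day 3 then compares those still alive, and a classical repeated-measures model with two time points gets no change score from the others. Those lost this way are likely to be the sickest. The withdrawal rules in the Design section also let researchers remove patients whose condition worsens markedly, which can add to the losses.

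Two consequences follow. The effect size and SD handed to the full trial apply to day-3 survivors and not to everyone randomized. And if early mortality differs between arms, the arm with more deaths can show the better day-3 mean.

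The stays have a related weakness. Treated as a plain duration, a stay that ends in death on day 2 ranks as more favourable than one that ends in recovery on day 10.

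Separately, if outcome collection really ends at day 28, hospital mortality and hospital stay cannot be completed for anyone still an inpatient, and the tests named do not allow for censoring.

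**Working it through.** **The plan's own figure.** 20 per group with 20% dropout: 20 / (1 − 0.20) = 25 per group, and 2 × 25 = 50. This matches the stated total and is not in dispute.

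The article gives no mortality, SOFA or length-of-stay figures. Every input below is therefore an assumption, shown over a range.

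**1. Patients without a day-3 value.** Let m be 28-day mortality and f the share of those deaths before day 3. The expected number is 50 × m × f, and the chance of at least one is 1 − (1 − mf)^50.

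| m | f | Expected of 50 | Chance of at least one |
|---|---|---|---|
| 0.20 | 0.20 | 2.0 | 0.87 |
| 0.30 | 0.30 | 4.5 | 0.99 |
| 0.40 | 0.40 | 8.0 | >0.99 |

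**2. Effect on day-3 SOFA.** Assume a latent day-3 score with mean 8 and SD 4 in both arms, so no treatment effect. Early death takes the fraction p with the highest value of score plus independent noise (SD 4). The correlation between the score and this sum is 4/√32 = 0.707. The mean among those observed is 8 − 4 × 0.707 × φ(z)/(1 − p), where z is the upper p-point of the normal distribution.

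- p = 0.15: 8 − 2.828 × 0.2332/0.85 = 7.22
- p = 0.05: 8 − 2.828 × 0.1031/0.95 = 7.69
- p = 0.10 in both arms: 7.45 against 7.45

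With 15% against 5% early deaths, the arm with more deaths looks better by 0.47 points (0.47/4 = 0.12 SD) although no effect exists. A simulation of 1,000,000 per arm gave 7.23 against 7.70, the same difference. With 20% against 4% it gave 7.01 against 7.75, a difference of 0.74. With equal early deaths there is no difference between arms.

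**3. Effect on ICU stay.** Illustration: survivors stay 10 ICU days, deaths occur on ICU day 5, and mortality is 30% against 50%.

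- Mean stay: 0.7 × 10 + 0.3 × 5 = 8.5 days, against 0.5 × 10 + 0.5 × 5 = 7.5 days
- ICU-free days to day 28 (survivors 28 − 10 = 18, deaths 0): 0.7 × 18 = 12.6, against 0.5 × 18 = 9.0

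Raw stay favours the arm with more deaths; free days do not. The simulation used log-normal stays (log-SD 0.6) and log-normal times to death (log-SD 0.8):

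| Survivor median stay | Median time to death | Mortality | Mean stay (days) |
|---|---|---|---|
| 10 d | 4 d | 30% vs 30% | 9.76 vs 9.76 |
| 10 d | 4 d | 30% vs 40% | 9.75 vs 9.02 |
| 20 d | 6 d | 20% vs 40% | 20.6 vs 17.3 |

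**4. Inpatients at day 28.** With log-normal hospital stay of median M and log-SD s, the share beyond day 28 is 1 − Φ(ln(28/M)/s).

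- M = 14, s = 0.5: ln 2 / 0.5 = 1.386, giving 8%
- M = 21, s = 0.7: ln(1.333)/0.7 = 0.411, giving 34%

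That is about 4 to 17 of 50 patients, if the clause does end collection at day 28.

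**The case against.** **Silence is not an error.** The article never says that deaths are scored as discharges or dropped from day-3 comparisons. A detailed rule may sit in an analysis plan or full protocol that is not shown. This stands, and it limits the weight of the point. But the article does fix the two measurement days, the tests and the effect-size aim, and together these leave early deaths without a day-3 value.

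**Death is not hidden.** A reader might infer that the plan ignores death and could pass off a harmful treatment as beneficial. The document does not support that. 28-day all-cause mortality is a secondary endpoint, and ICU and hospital mortality stand in the same sentence as the stays, so a mortality difference would be reported beside a shorter stay. Feasibility is the primary endpoint and is not touched. The exclusion of patients not expected to survive 28 days because of end-stage or uncorrectable disease also lowers the number of early deaths, without removing them.

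**The day-28 clause is ambiguous.** It sits in the definition of dropout and may mean only that nothing is collected once a patient is lost. It is tempting to say that this second reading contradicts the intention-to-treat sentence. It does not: defining who is lost is compatible with keeping those patients in the analysis as randomized. Nor is it established that collection stops at day 28. That is the nearer grammatical reading, and the adverse-event window agrees with it, but that window is a separate safety rule and the schedule figure is not shown.

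**Length of stay is exploratory.** A reader might count it among the outcomes whose suitability the pilot is to judge. That aim names the secondary measures only, so it covers SOFA, APACHE II and the markers but not the stays.

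**Worst-rank scores give no mean or SD**, which a planning pilot needs. This stands, and the fix allows for it.

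**Conclusion.** The point holds in limited form and should be settled before analysis. It does not threaten the trial.

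The day-3 part matters most. Under the assumed mortality range, 2 to 8 of 50 patients would have no day-3 value, and the effect sizes passed to the full trial would describe survivors only. That restriction applies even when mortality is equal. Bias between arms is conditional: it arises only if early mortality or its timing differs. The 0.47-point SOFA difference and the 8.5 against 7.5 day stay are illustrations of that case and not estimates for this trial.

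The length-of-stay part follows the same logic but concerns exploratory outcomes. The day-28 part is a conflict on one reading of an ambiguous clause. The Outcomes and Data acquisition sections must be reconciled, whichever reading was meant.

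**What to change.** 1. Compare day-3 SOFA and APACHE II by rank-sum test with death before day 3 ranked worst. Also report survivors' mean and SD for planning.
2. For mHLA-DR, the CD4+/CD8+ ratio and the inflammation markers, report deaths before day 3 by arm beside the survivors' estimate.
3. Analyse ICU-free and hospital-free days to day 28, scoring death by day 28 as 0. Tabulate raw stay separately for survivors and for those who died.
4. State that ICU and hospital mortality and stay are truncated at day 28, or state that they are followed to discharge. Reword the dropout sentence to match.

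The cost is mainly wording. The sample size does not change, items 1 to 3 use information that the listed outcomes already require, and the article already names a rank test. Following patients to discharge under item 4 would add data collection for those still in hospital after day 28, whereas truncation would leave later in-hospital deaths uncounted. Rank-based and free-day results are less familiar and mix death with duration, so mortality by arm should be shown beside them.

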#### Inclusion criteria

The inclusion criteria for the observational study [15] are as follows:
Aged between 18 and 85Documented or suspected infectionTwo of the following induced by the infection:
rectal temperature between 38 °C and 36 °Cheart rate >90 beats per minuterespiration rate >20 breaths per minute, partial pressure of carbon dioxide in arteries pa CO_2_ < 32 mmHg, or requiring ventilationwhite blood cell count >12 × 10^9^ L^-1^ or <4 × 10^9^ L^-1^, or immature forms of white blood cells >10%One of the following:
arterial hypotension (systolic blood pressure, SBP < 90 mmHg, mean arterial pressure <65 mmHg, or SBP decrease >40 mmHg in adults or vasopressor-dependent to maintain SBP ≥ 90 mmHg or mean arterial pressure ≥ 65 mmHg) persisting for 1 hour or more in spite of adequate fluid resuscitationoxygenation index ≤300pH ≤ 7.30 or base excess ≤ –5.0 mmol L^-1^ with hyperlactatemia (≥3 mmol L^-1^)acute oliguria (urine output <0.5 mg kg^-1^ h^-1^ for at least 2 hours), creatinine increase >2 mg dL^-1^ within 48 h, or requiring renal replacement therapyhyperbilirubinemia (plasma total bilirubin > 2 mg/dL or 35 μmol L^-1^)platelet count < 10 × 10^12^ L^-1^international normalized ratio >1.5 or activated partial thromboplastin time >60 s

The inclusion criteria for the interventional study are as follows:
Meet all the criteria for the observational part*Yin* syndrome, presenting some of the following [16]:
sudden drop of body temperature or cold extremitiesfatiguepale complexiondull paincold sweat or sticky sweatdull purplish or pale tonguefaint or deep slow pulse

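### Renal replacement therapy, allowed at entry and during the trial, clears the two markers that form the renal function test, so the day-3 creatinine and urea comparison could mask or even invert renal harm

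*Protocol article*

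**What the plan says.** All references are to the protocol article.

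- **Inclusion criteria.** Needing RRT is one way to meet the organ-dysfunction requirement of the observational study. The interventional study carries this over: "Meet all the criteria for the observational part". The exclusion criteria contain no renal item.
- **Standard therapy.** Both arms may receive "mechanical ventilation, glucose control, sedation or analgesia, renal replacement therapy, and adequate nutrition".
- **Outcomes.** The safety laboratory list begins "Safety outcomes include a complete blood count, a general urine analysis, C-reactive protein (CRP), liver function tests" and ends with "a renal function test (blood urea nitrogen (BUN) and serum creatinine (Scr)), all of which will be performed at days 0 and 3". Urea and creatinine are the only tests given the label of renal function.
- **Statistical analysis.** "An unpaired Student’s *t*-test will be used for normally distributed quantitative variables", with a Wilcoxon test otherwise and a repeated-measures general linear model for biological metrics over time. None of these carries a condition for RRT.
- **Data acquisition and assessment of biological data.** The further clinical data named are age, gender, infection source and co-morbidities. SOFA and APACHE II are collected at enrollment and three days later. On adverse events: "All adverse events after enrollment to the 28th day after enrollment, regardless of whether they are related to the intervention, will be recorded", and "All severe adverse events and unexpected adverse events will be reported to the ethics committee within 1 day".

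**The concern.** The article admits and treats patients with a therapy that acts directly on its renal function markers, and the harm being monitored is what brings that therapy on. This differs from the general noise of intensive care. A patient whose kidneys fail after randomization and who starts RRT on day 1 or 2 may reach day 3 with creatinine near or below the day-0 value. The same patient without RRT would show a clear rise. The worst renal outcomes are thus pulled towards normal, and more so in whichever arm has more of them.

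The Outcomes section says the pilot will be used to develop the protocol for further trials. A reassuring day-3 creatinine table is the kind of safety result that would be taken forward, and its reassurance could be false.

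**Working it through.** **The plan's own figure.** The article states no renal effect size, margin or power, so no renal figure can be reproduced. The sample size can: 20/(1 − 0.20) = 25 per arm, 50 in total, as stated. The point does not dispute it.

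Everything below uses assumed inputs that are not in the article.

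**1. One patient.** The model is dC/dt = (G − (K_res + K_RRT)·C)/V. Assumed: V = 420 dL, K_res = 3 dL/h (5 mL/min), G = 600, 800 or 1000 mg/day, and RRT from 24 h at K_RRT = 12.25 or 17.5 dL/h. Creatinine at 72 h, mg/dL, for the three values of G:

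| Day-0 value | No RRT | RRT 12.25 dL/h | RRT 17.5 dL/h |
|---|---|---|---|
| 3.0 | 5.14 / 6.26 / 7.38 | 2.02 / 2.55 / 3.08 | 1.47 / 1.88 / 2.29 |
| 1.5 | 4.25 / 5.36 / 6.48 | 1.80 / 2.33 / 2.86 | 1.35 / 1.76 / 2.17 |

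From 3.0, a rise of about 2–4 becomes a fall of up to about 1.5, or no change. From 1.5, the harm is mostly masked rather than reversed.

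**2. When does the arm difference change sign?** Let h be the rise in a harmed patient without RRT, d the fall in a harmed patient on RRT, and s the share of the extra harmed patients who are on RRT at day 3. With no change in unharmed patients, the sign flips at s = h/(h + d).

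- Assume a baseline of 200–300 µmol/L and a 30–50% fall on RRT, so d = 60–150, with h = 100–200. The lowest threshold is 100/(100 + 150) = 40%. The highest is 200/(200 + 60) = 77%.
- With 2 to 6 extra harmed patients of 25 on SNT (8–24%), the difference in mean change (SNT minus control) if all of them are on RRT runs from −0.08 × 60 = −4.8 to −0.24 × 150 = −36 µmol/L. If none are, it runs from +0.08 × 100 = +8 to +0.24 × 200 = +48 µmol/L.
- As a second set, assume mean changes of −0.8 mg/dL on RRT and −0.1 in unharmed patients, with h = 2–4 mg/dL from step 1. Then s = (h + 0.1)/(h + 0.8), giving 2.1/2.8 = 75% to 4.1/4.8 = 85%.

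**3. A whole trial at the extreme.** Simulate 25 per arm with every harmed patient on RRT. The change is −0.8 (SD 0.8) on RRT and −0.1 (SD 0.5) otherwise.

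| RRT, SNT vs control | Mean difference, mg/dL | SNT looks better (sign only) | SNT better with P < 0.05 |
|---|---|---|---|
| 20% vs 20% | 0.00 | 50% | about 2.5% |
| 40% vs 20% | −0.14 | 76% | about 10% |
| 40% vs 10% | −0.21 | 87% | about 19% |

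The mean differences follow directly: 0.20 × (−0.7) = −0.14 and 0.30 × (−0.7) = −0.21.

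**4. New RRT as its own outcome.** Power with 25 per arm, two-sided 0.05, is 24% for 20% vs 36% and 44% for 20% vs 44%.

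**The case against.** **Other routes to a renal signal exist.** A reader might infer that renal safety rests only on creatinine and urea. The article does not support that. Urine analysis is a safety outcome at the same two days. All adverse events are recorded to day 28, so kidney failure needing RRT could be captured there. This stands. What remains is narrower: neither route corrects the creatinine and urea comparison, and the article does not name new RRT as an outcome to be counted by arm. SOFA and APACHE II help little, because they are secondary endpoints and their creatinine input has the same weakness.

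**Inversion is not the expected result.** A reader might also infer that renal harm would read as improvement. This needs most of the harmed patients to be on RRT at day 3. Below that share the comparison still points towards harm, though weakened. A patient on RRT at both days gives largely uninformative values, not a false improvement. The 76% and 87% count only the sign, which is 50% with no difference, and they assume that no harm occurs without RRT. This stands, and the claim is therefore that harm could be masked or inverted.

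**The stakes are limited.** The primary endpoint is feasibility. The stated success criteria are at least 50% recruitment and no more than 20% dropout, and no decision rule uses renal results. This lowers the weight of the point but does not remove it.

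**The detail may sit elsewhere.** A full protocol, an analysis plan or the case report form may hold an RRT field or a handling rule. That is possible, and silence here does not prove absence. But the article itself fixes the renal function test and its timing alongside its own RRT provisions, and that combination is the problem.

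**Conclusion.** The point holds as a limited one. The article makes day-0 and day-3 urea and creatinine its renal function test while allowing, at entry and during treatment, a therapy that clears both. The comparison under the general analysis rules could mask renal harm. It could invert it if most of the harmed patients are on RRT at day 3: roughly 40–77% or 75–85% of them, depending on the values assumed. Even in the extreme simulation, a nominally significant false benefit appears in only about 10–19% of trials. Every RRT share and kinetic value here is an assumption. The article supports the possibility and the mechanism, not a predicted size. It is worth correcting because the correction is cheap, not because the trial's primary conclusion depends on it.

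**What to change.** - **Outcomes, and Data acquisition and assessment of biological data.** Record RRT status at day 0 and any new start up to day 28, the existing adverse event window. Report as a safety outcome, by arm, the number with new RRT among those not on RRT at day 0, with deaths shown alongside.
- **Statistical analysis.** Summarise creatinine and urea only in patients with no RRT from day 0 through the day-3 sample. Leaving out only those on RRT at day 0 is not enough, because the lowered values of patients with new RRT would stay in. Always show beside this summary the counts per arm on RRT at day 0, with new RRT, and dead before day 3, because the restricted group is selected after randomization.
- **If one comparison is wanted.** Among patients not on RRT at day 0, rank new RRT or death by day 3 as the worst category and the others by creatinine change. Use the Wilcoxon test already planned.

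**Cost.** One extra field taken from the chart, with no new test and no more patients. Fewer patients contribute to the creatinine and urea summary. With 25 per arm the power for new RRT is low (24–44% in the cases shown), so the result should be presented descriptively.
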